7.2 Safety Assessment

Collect and record AE anytime it occurs. Physical examination, vital sign measurement and laboratory tests such as hematology, urinalogy, blood biochemistry test will be performed.

7.3 MRI assessment

MRI was performed with 1.5 Tesla (Siemens, Erlangen, Germany) systems using propriate suface coils. Sequences including T1-weighted spin echo (T1WSE) and short-tau inversion recovery (STIR) were acquired in a coronal plane titled parallel to the long axis of the SJ joint with 3-4 mm slice thickness and 12-15 slices acquired.

SPARCC of SIJ and spine

SPARCC SIJ scores were based on the measurement of six consecutive slices, with largest score of 12 for edema, intensity and depth per slice and a total score of 0-72. Three consecutive slices of whole spine were measured and six most severely affected discovertebral units per slice were chosen to give a maximal score of 6 for edema, intensity and depth in one discovertebral unit for SPARCC spinal score. A total of 0-108 score was calculated and with a higher score indicating greater inflammation.

SPARCC MRI Sacroiliac Joint Structural Score

SPARCC SSS was used to assess the structure lesions basing on T1WSE sequences. Four kinds of lesions are assessed based on five consecutive slices through the SIJ. Fat metaplasia is defined as an increased signal in bone marrow on T1WSE and the lesion has to demonstrate homogeneous signal with more than 1 cm in depth from the joint surface. Erosion is defined as the full-thickness loss of the dark appearance of either iliac or sacral cortical bone at its anticipated location and loss of the normal bright appearance of adjacent bone marrow. Backfill is defined as complete loss of iliac or sacral cortical bone at its anticipated location and increased signal that is clearly demarcated from adjacent normal marrow by irregular dark signal reflecting sclerosis at the border of the eroded bone. Ankylosis is defined as bone marrow signal on T1WSE sequences extending between the sacral and iliac bone marrow with a full-thickness loss of the dark appearance of the iliac and sacral cortical bone. The presence/absence of lesions is scored using an online data entry system in SIJ quadrants (fat, erosion) or halves (backfill, ankylosis) with a scoring range of 0-40 for quadrants lesions and 0-20 for halves lesions.

7.4 Radiographic assessments

The modified Stroke Ankylosing Spondylitis Score (mSASSS) was used to assess the structural change of AS patients. It assesses the anterior part of the cervical and lumbar spine (from the lower corner of T12 to the upper corner of S1 and from the lower corner of C2 to the upper cornor of T1) as follows: 0= normal; 1= erosion, sclerosis or squaring; 2= syndesmophytes; 3=bridging syndesmophytes (the total score ranges from 0 to 72).

8.Subject Withdrawal

Once a subject is randomized to investigational product, the subject’s vital status will be tracked for the duration of the study. Subjects may choose to discontinue use of investigational product at any time but full accountability at the end of the study is required of all subjects.

If a subject withdraws or discontinued for any reasons prior to last visit, e.g. to withdraw IFC, early withdraw from the study due to AE etc., an early end of treatment assessments listed in ”Early end of treatment” of the study flow chart at the last visit must be completed.

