2.2 Outcomes

There are two primary outcomes in this study. The first one is to compare the Spondyloarthritis Research Consortium of Canada (SPARCC) score of SIJ and spine from baseline to week 52 in three treatment groups in active AS patients. The co-primary outcome is to compare the Assessment of Spondyloarthritis International Society (ASAS) 20 response rate of three treatment groups at week 52.

Secondary outcomes include ASAS40, ASAS70, ASAS5/6 response rate, ASAS partial remission, Ankylosing Spondylitis Disease Activity Score (ASDAS) remission and ASDAS low disease activity, Bath Ankylosing Spondylitis Disease Activity Index (BASDAI), Bath Ankylosing Spondylitis Functional Index (BASFI), Bath Ankylosing Spondylitis Metroloty Index (BASMI), Masstricht Ankylosing Spondylitis Enthesitis Score (MASES) and safety outcomes.

3.Study design

This is a prospective, open label, active controlled, parallel group study. A total of 150 active AS patients will be randomized in a 1:1:1 ratio into the following three treatment groups: celecoxib 200mg twice a day, etanercept 50mg weekly, celecoxib 200mg twice a day plus etanercept 50mg weekly for 52 weeks. This study will be registered in the Clinical Trials.

4.Subject Selection

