8.1 Withdrawal from Investigational Product

A subject may voluntarily discontinue investigational product at any time. The investigator may also, at his or her discretion, discontinue a subject from receiving investigational product at any time. Every effort should be made by the investigator to keep the subject in the study. Subjects who are withdrawn from investigational product will be replaced.

The primary reason for subject withdrawal from investigational product will be recorded in the CRF. Primary reasons for withdrawal will be categorized as:

Adverse event
Withdrew consent
Lost to follow-up
Lack of efficacy
Subject reached protocol-defined stopping criteria
Study closed/terminated
Investigator discretion

AS exacerbation may be a reason for withdrawal under lack of efficacy. Specific regard should be given to distinguish withdrawals due to an adverse event and lack of efficacy.

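### Section 8 does not separate stopping study drug from leaving the study, so week-52 co-primary data are not clearly required from subjects who stop drug

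*Protocol*

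**What the plan says.** Section 8 (Subject Withdrawal) opens by saying that, once a subject is randomised, "the subject’s vital status will be tracked for the duration of the study". It allows subjects to stop product whenever they choose, but adds that "full accountability at the end of the study is required of all subjects". The term is not defined. The close-out rule follows: "If a subject withdraws or discontinued for any reasons prior to last visit", with the examples "e.g. to withdraw IFC, early withdraw from the study due to AE etc", the assessments in the early end-of-treatment column "of the study flow chart at the last visit must be completed".

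Section 8.1, which concerns withdrawal from product, says "Every effort should be made by the investigator to keep the subject in the study", and in the next sentence that subjects withdrawn from product are replaced. Its list of primary reasons for stopping product includes adverse event and lack of efficacy. It also includes withdrawn consent, loss to follow-up and study closure.

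Section 2.2 sets both primary outcomes at week 52: the change in SPARCC score of the sacroiliac joints and spine from baseline to week 52, and the ASAS "20 response rate of three treatment groups at week 52". The timetable in section 6 places MRI at screening, week 24, week 52 and early end of treatment. Efficacy is assessed at every visit. There is no column or note for subjects who are off drug but still in the study.

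**The concern.** Stopping treatment and leaving the study are different events, and a trial with an outcome at a fixed time needs separate rules for them. Section 8 gives one rule that can be read to cover both. If a site treats the early end-of-treatment visit as the subject's last, that subject has no week-52 value for either co-primary outcome. The early visit records status near the time of stopping, at a time that varies between subjects, so it does not replace week 52.

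Subjects stop for reasons such as lack of efficacy (section 8.1 mentions AS exacerbation) or adverse events. The trial is open label and compares each of two drugs alone with their combination, so these reasons may well occur at different rates in the three arms. The resulting missing data would be related to outcome and possibly unbalanced. An analysis plan can choose how to handle missing values, but it cannot recover visits that were never made.

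**Working it through.** The protocol gives no figure to reproduce here: section 10 states no power, effect size or discontinuation rate. The check is a comparison of the texts.

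1. **Does the close-out rule cover stopping drug alone?** The trigger is "If a subject withdraws or discontinued for any reasons prior to last visit". The sentence just before it uses the verb discontinue for product use, and the trigger is not limited by reason. On that reading, stopping drug is included. The two examples, "e.g. to withdraw IFC, early withdraw from the study due to AE etc", both describe leaving the study, which supports the narrower reading. Examples do not limit a rule that applies to any reason, so both readings remain open.

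2. **What does the rule require?** One set of assessments. The column is named for the end of treatment, but the assessments are made "of the study flow chart at the last visit must be completed". The two events meet in this sentence.

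3. **Does section 8.1 separate them?** Only in its heading. Its reasons for stopping product include events that end participation in the study. It asks the investigator to retain the subject, then provides for replacement, and names no visit for a retained subject.

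4. **Does another sentence secure the week-52 assessment?** Vital status is tracked for every randomised subject, but it is not an efficacy measure. The accountability clause in section 8 could be meant to secure the assessment, but it is undefined. The timetable lists weeks 24 and 52 without limiting them to subjects on drug, and without saying that they continue after an early end-of-treatment visit.

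5. **What would be missing under the close-out reading?** Take an illustrative subject who stops at week 8. MRI would exist at screening and at the early visit: 2 rounds, with none at week 24 or week 52. ASAS components would exist at the visits up to the early one. A subject who stops between weeks 24 and 52 would have screening, week 24 and the early visit: 3 rounds, with none at week 52.

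6. **What follows for the analysis?** Section 10 defines the ITT population as randomised subjects with at least one dose and an efficacy evaluation after baseline. A subject who stops early and has such an evaluation stays in that population but has no week-52 outcome. With 150 randomised 1:1:1, each arm has 150 / 3 = 50 subjects, so each subject closed out removes 1 / 50 = 2% of that arm's week-52 outcomes before any replacement. A replacement adds another subject's outcome and does not supply the missing one. How many subjects would be affected is unknown.

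**The case against.** The strongest reply is that the protocol is coherent if the close-out rule is read through its examples. The last visit is then the final visit of someone who leaves the study, a subject who only stops drug stays on the timetable, and the retention sentence in section 8.1 says just that. The accountability clause points the same way. This reading is tenable, so it would be wrong to infer that the text flatly contradicts itself, or that it says week-24 and week-52 data are not collected after stopping. No sentence says so. What stands is that the text does not choose between the readings, and different sites could follow different ones.

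A reader might also draw three further inferences that the document does not support:

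- **Only vital status is tracked after stopping.** The sentence applies to every randomised subject from randomisation and is not worded as exclusive.
- **Adverse events after stopping are lost.** Section 7.2 asks for adverse events to be recorded whenever they occur.
- **A combination subject who stops one of the two drugs is closed out.** The text does not address that case.

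It can also be said that the SPARCC mixed model uses whatever data a subject has, and that missing week-52 ASAS20 may be handled in an analysis plan not shown. Both are fair. They concern how missing data are analysed, whereas which visits are made is for the protocol to settle.

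**Conclusion.** The point holds as an ambiguity with a real consequence. Sections 8 and 8.1 do not separate stopping drug from leaving the study, and a site that reads the close-out rule to cover stopping drug can close out a subject with no required week-24 or week-52 SPARCC or ASAS20.

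The size and direction of any bias cannot be derived from the document. They depend on how many subjects stop in each arm, how those subjects fare afterwards, and how missing week-52 values are handled, none of which the protocol states. It would be tempting to put a number on the distortion by comparing subjects who stay on drug with all randomised subjects. Every input would have to be assumed, and an analysis of stayers only is not the protocol's main analysis.

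The conclusion assumes only that some subjects stop drug before week 52 while still willing to attend, and that at least some sites follow the broader reading. The change is worth making because it is cheap and prevents missing data that no later analysis can restore.

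**What to change.** Reconcile sections 8 and 8.1 by stating two cases:

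- **Stops study drug, consent not withdrawn.** The subject has the early end-of-treatment assessment, then continues the scheduled assessments through week 52, at least the ASAS components and MRI at whichever of weeks 24 and 52 are still to come. The subject is analysed in the arm as randomised.
- **Withdraws consent or is lost to follow-up.** Only these end data collection.

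Record the stop date of celecoxib and of etanercept separately, and any treatment started later. Define the accountability clause in these terms. Word the replacement sentence so that replacing a subject does not end that subject's follow-up or remove the subject from the analysis. Add a note to the timetable in section 6. The change concerns data collection only and leaves the rules on treatment as they are.

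**Cost.** This is a protocol wording change with no additional subjects. Sites must keep contact with off-drug subjects, some of whom will attend without receiving study treatment. Some will also have one more imaging round than planned. The plan has 3 MRI rounds (screening, weeks 24 and 52), and an early visit that does not coincide with one of them makes 3 + 1 = 4. X-rays of the sacroiliac joints and spine follow the same timetable.

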8.1 Withdrawal from Investigational Product

A subject may voluntarily discontinue investigational product at any time. The investigator may also, at his or her discretion, discontinue a subject from receiving investigational product at any time. Every effort should be made by the investigator to keep the subject in the study. Subjects who are withdrawn from investigational product will be replaced.

The primary reason for subject withdrawal from investigational product will be recorded in the CRF. Primary reasons for withdrawal will be categorized as:

Adverse event
Withdrew consent
Lost to follow-up
Lack of efficacy
Subject reached protocol-defined stopping criteria
Study closed/terminated
Investigator discretion

AS exacerbation may be a reason for withdrawal under lack of efficacy. Specific regard should be given to distinguish withdrawals due to an adverse event and lack of efficacy.

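### Section 8.1 replaces every subject withdrawn from study drug, which contradicts 150 randomised 1:1:1 and leaves the allocation and analysis of replaced subjects undefined

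*Protocol*

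**What the plan says.** Section 3 of the protocol fixes the size and allocation: "A total of 150 active AS patients will be randomized in a 1:1:1 ratio". It also describes the design: "This is a prospective, open label, active controlled, parallel group study". One of the two primary outcomes in Section 2.2 is the ASAS20 "response rate of three treatment groups at week 52"; the other is the SPARCC score from baseline to week 52.

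Section 8.1 allows the subject to stop study drug voluntarily, and allows the investigator to "discontinue a subject from receiving investigational product at any time". It then gives two instructions in succession: "Every effort should be made by the investigator to keep the subject in the study", and "Subjects who are withdrawn from investigational product will be replaced". The reasons listed below them include adverse event, lack of efficacy and investigator discretion, and the section adds: "AS exacerbation may be a reason for withdrawal under lack of efficacy".

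Section 8 tracks vital status, requires full accountability for all subjects at the end of the study, and asks for an early end-of-treatment assessment "If a subject withdraws or discontinued for any reasons prior to last visit". In the Section 6 timetable that assessment includes efficacy, MRI and X-ray.

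Section 10 analyses efficacy in an ITT set of randomised subjects who took at least one dose and had an efficacy evaluation after baseline. The primary analysis is repeated in a PP set of completers without protocol violations.

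**The concern.** Replacement is triggered by events after randomisation, some of which are consequences of the assigned treatment. Three things are left unsettled.

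- **Number.** The protocol cannot keep every original subject, add a replacement for each withdrawal, and still randomise 150.
- **Allocation.** Section 5.1 describes one randomisation step and says nothing about replacements. If a replacement takes the vacated arm, an open-label site knows the assignment before it enrols the patient, and it can create the vacancy through investigator discretion.
- **Analysis.** No section says whether a replaced subject stays in the comparison. If not, the arm that loses more treatment failures looks better than it is, and the contrast of the combination with each monotherapy is distorted.

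The first two are matters of trial conduct. An analysis plan cannot undo extra enrolment or a foreseeable assignment.

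**Working it through.** **Inputs.** From Section 3: 150 randomised, 1:1:1. The protocol gives no withdrawal or response rates, so those below are assumptions, shown as ranges.

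**1. The plan's own figure.** 150 / 3 = 50 per arm.

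**2. Total randomised if originals are kept.** With withdrawal proportion d and one replacement each, N = 150 × (1 + d). If replacements also withdraw and are replaced in turn, N = 150 / (1 − d), rounded up.

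| d (assumed) | One replacement each | Refilled until every slot completes |
| --- | --- | --- |
| 10% | 165 | 167 |
| 20% | 180 | 188 |
| 30% | 195 | 215 |

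**3. Arm sizes if replacements fill the vacated arm.** With 30% withdrawal in one arm and 10% in another: 50 × 1.30 = 65 against 50 × 1.10 = 55. The 1:1:1 ratio is lost.

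**4. Bias if replaced subjects leave the analysis.** Suppose two arms have the same true ASAS20 rate r among all randomised, and withdrawn subjects are non-responders. If each slot is refilled until it completes, the apparent rate is r / (1 − w), where w is the arm's withdrawal proportion. With w = 30% and 10%:

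| r | Arm with 30% withdrawal | Arm with 10% withdrawal | Spurious difference |
| --- | --- | --- | --- |
| 40% | 0.40/0.70 = 57.1% | 0.40/0.90 = 44.4% | 12.7 points |
| 50% | 0.50/0.70 = 71.4% | 0.50/0.90 = 55.6% | 15.9 points |
| 60% | 0.60/0.70 = 85.7% | 0.60/0.90 = 66.7% | 19.0 points |

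The advantage goes to the arm with more withdrawals. With 50 per arm and a two-sided 5% test, the chance of significance in that direction is Φ[(difference − 1.96 × SE0) / SE1], where SE0 uses the pooled rate and SE1 the separate rates. It is about 24%, 38% and 61% for the three rows. At r = 40%, for example, SE0 = 0.1000 and SE1 = 0.0992, so Φ[(0.1270 − 0.1960)/0.0992] = Φ(−0.70), or about 24%.

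**5. Sensitivity to the assumptions.**
- With 20% versus 10% withdrawal, the spurious difference is 5.6 to 8.3 points over the same range of r.
- With equal withdrawal there is no spurious difference, though both rates are inflated.
- If originals leave but each slot is refilled only once, the apparent rate is r + w × r = r(1 + w). With 30% versus 10% the difference is r × 0.20, or 8 to 12 points.

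**6. If originals stay in the ITT set.** Count withdrawals as non-response and draw replacements from the same population. Originals and replacements then both have expected rate r in each arm, and the spurious difference is 0.

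**The case against.** The strongest objection is that Section 10 already protects the main analysis. Its ITT set keeps randomised subjects who were dosed and evaluated after baseline, and neither withdrawal nor replacement is a ground for exclusion. A subject who attends the early end-of-treatment visit meets the evaluation condition. On that text, replacement adds subjects and removes none. The PP set is restricted to completers by its own definition, with or without replacement. This stands, and it makes the bias in steps 4 and 5 conditional.

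A reader might infer that subjects off drug are followed for vital status only. The protocol does not say so: Section 8 also requires full accountability, and Section 8.1 asks that they be kept in the study. It sets no visit schedule after drug is stopped, but that is a different matter.

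It is also fair to say that no section sends a replacement to the vacated arm. Section 5.1 could be read as ordinary randomisation for everyone, so foreseeable assignment is a possibility left open, not a stated procedure. Arm sizes that drift with all originals kept do not by themselves bias the comparison.

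The objection does not reconcile Section 8.1 with the total of 150, and it does not say what becomes of a replaced subject.

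**Conclusion.** The replacement rule contradicts the fixed number randomised and sits badly with the instruction, in the sentence before it, to keep the same subject in the study. Under assumed withdrawal of 10% to 30%, the excess over 150 is 15 to 45 subjects with one replacement each.

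It is tempting to conclude that the week-52 comparison becomes one of patients who tolerate and respond to treatment. The documents do not support that as a certainty. It follows only if replacement means substitution in the analysis, which the protocol neither states nor rules out. On that reading, the spurious difference between equally effective arms is about 13 to 19 points, assuming 30% versus 10% withdrawal, withdrawn subjects as non-responders, and slots refilled until they complete. With originals kept in ITT and counted as non-responders it is zero. Selection of completers applies to the PP set in any case.

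How missing week-52 data are handled may be set in the analysis plan and is not part of this finding.

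**What to change.** Delete the replacement sentence in Section 8.1. State instead that 150 subjects will be randomised, that randomised subjects will not be replaced, and that all remain in their randomised arm in the ITT analysis. Add that week-52 assessments will be sought from subjects who have stopped study drug, which gives effect to the existing instruction to keep them in the study.

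If added subjects are considered essential, the lesser alternative is to state that replaced subjects stay in the ITT set, that each added subject is newly randomised with concealed allocation, and what the total then is.

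The cost is a short protocol amendment and continued assessment of subjects off drug. The downside is somewhat fewer on-treatment completers.

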8.2 Screen Failures

A subject who has at least one study procedure performed signing a consent form, and is assigned a subject identifier but is not randomized is classified as a screen failure. The following information on subjects who are not randomized must be collected in the CRF:

Date screened

Subject identification number

Demography (race, age, and gender)

Reason subject failed Screening

Any Serious Adverse Events (SAEs) related to study procedures or concomitant medications, that occurred after signing the informed consent

A subject who is classified as a screen failure cannot be re-screened.

9.Adverse Event Reporting

Timely, accurate, and complete report and analysis of safety information are crucial for the protection of subjects, investigators, and the sponsor in the clinical trials.

